**2.3.4 Nitric oxide is stimulated on cervix during labour**

The NO represents the end of the metabolic pathway in cervical ripening being accompanied by prostaglandin biosynthesis, and a high concentration of metabolic products of nitric oxide (NOx) have been identified in vaginal secretions during preterm labour.49 Although the source of these metabolites is unknown, it is possible that inflammatory cells infiltrating the as well tissue on the cervix, and this may be responsible for NO synthesis. The NO can induce cell death by apoptosis,27,50 but also activate MMPs.51,52 Thus, overproduction of NO can be related to cervical ripening, fragility of membranes and subsequent labour in premature birth.

Endogenous NO production was detected in the cervix of different species being negatively regulated during pregnancy and overregulated in labour. Studies in animals show that NO is associated with the induction of cervical ripening still high release of the molecule during labour.53,54 The NO share with TNF-α ability to initiate and/or block process of apoptosis depending on the cell cycle and its multiple factors that so far have not been identified.50 Although NO is an apoptotic substance that it can turn of the cellular cycle also permit the reorganization of collagen.53,55 Furthermore, NO in harmony with PGE2 can induce local vasodilation increasing vascular permeability and infiltration of leukocytes directly regulating the activity or production of MMPs.56,57Although, Ledingham et al. (1999) showed that the secretion of MMP-2 and MMP-9 in cervical fibroblasts were not covered by the overproduction of NO.58

***2.3.5 Endogenous synthesis of nitric oxide***

Endogenous NO is synthesized from the amino acid L-arginine and this synthesis is catalyzed by the enzyme nitric oxide synthase (NOS) in the presence of molecular oxygen, nicotinamide adenine dinucleotide phosphate (NADPH) and various cofactors tetrahidrobiopterinos. In addition, NO production is stimulated by intracellular calcium binding to calmodulin in endothelial cells. All three isoforms of nitric oxide synthase (nNOS, eNOS and iNOS) are present in the human cervix.59-61 The neuronal nitric oxide synthase (nNOS or NOS I) which is located in the stroma and epithelial cells,61 the inducible synthase (iNOS or NOS II) first identified in neurons, activated macrophages and vascular endothelial and epithelial cells and stroma of the spindle cervical cells, and endothelial enzyme (eNOS or NOS III) identified in vascular endothelium.59

Originally, NOS was discovered as an enzyme activator which catalyzes the synthesis of nitric oxide from L-arginine.62 Bredt et al. (1991) were the first researchers to publish the molecular cloning of NOS, indicating the existence of three binding sites for oxidative cofactors (NADPH, FAD, FMN) and the consensus sequence for a binding site calmodulin.63 The carboxy terminal sequence of NOS is like the cytochrome P450 reductase, and indeed, in the cerebellum NOS can function as a cytochrome P450 reductase.64 The cDNA of eNOS was the last of the three isoforms that was cloned to be highly homologous to other.65 The eNOS is a single copy of the genome located at chromosome encoded 7q35-36 in humans.66 The genomic DNA encoding a 1294 aa protein with a molecular weight of 135 kDa and it is expressed in endothelial cells that line the vasculature of connective tissue. The chemical activity of NO produced by the NOS pathway lies in the fact activate path soluble guanylate cyclase (sGC) causing increased synthesis of cGMP resulting intracellularly which in turn induces relaxation of subendothelial smooth muscle cells, including the veins in the brain and heart, and inhibits the adhesion and aggregation of platelets.67 Only, NOS type I and III are expressed constitutively calcium and calmodulin dependent, and requires the formation of iNOS from novo synthesis and calcium independently is mediated by certain cytokines such as IFN-γ and TNF-α, bacterial lipopolysaccharide processes and oxidative stress and inflammation.68,69

The transgenic mouse model of the eNOS allowed to explore the role of the enzyme in the regulation of blood pressure and different localization in tissues.70-72 These studies show overexpression sites of eNOS in vascular smooth muscle cells of the heart, lung and uterus, with lower levels of expression in brain, cerebellum and liver. However, the production of NO by NOS action in the endothelium of the animals is observed clearly reduced when mediated by nitrogenous vasodilators. These animals show a permanent state of hypotension, but without the increase in the volume of urine excreted or increased heart rate.

By contrast, "knock-out" mice for eNOS gene show hypertension phenotype with changes in behavior, heart valves level abnormalities, and insulin resistance; also they have high sensitivity to contractile action ß-adrenergic agonist. From these studies it has proposed the dual role of endothelial nitric oxide synthase as it is involved not only in regulating blood pressure, but also in lipid homeostasis, glucose and angiogenesis.73-75

***2.3.6 Nitric oxide donors and cervical ripening***

The GTN referred to as nitroglycerin was added as a therapeutic agent of angina pectoris. Other organic compounds with nitrate ester functional group (-O-NO2) as isosorbide dinitrate and pentaerythritol tetranitrate have similar pharmacological properties and like GTN are prescribed to treat a variety of heart and vascular damages.76

Organic nitrates are reduced to produce NO, which lead the activation of guanylate cyclase. The GC catalyzes the conversion of GTP to cGMP concentrations by increasing intracellular levels that lead to smooth muscle endothelial cell relaxation.11-13,78-79 Therefore, activity of the nitrate ester is related to the metabolism of NO and bioreactive these products can also participate in the endogenous pathway of NO production to maintain vascular smooth muscle tone.14-16 Previous studies indicate that bioactivation of nitrate ester to NO may be an enzymatic process which involve the cytochrome P-450 and/or thiol groups that require glutathione (GSH) to reduction.80-84 Moreover, nitrate ester activation may be mediated by the flavoprotein associated with the cell membrane.85 During chemical intimacy between thiol groups and flavins (flavin mononucleotide, FMN, flavin adenine dinucleotide, FAD) is possible the catalysis nitrate ester by NAD(P)H to reduce to different nitrogen species, which are procursores of NO formation.86

Chemical studies provide evidence that organic nitrate ester can be reduced in the presence of nucleotides and pirimídicos flavins nitrite ester. At the biochemical level, it is possible that this first step in the activation of nitrate ester is able to integrate the transmembrane flavoproteins (removal of radicals contributing to oxidative stress) a way that the nitrites potencialice catalyst for the production of NO. However, because nitrate ester more stable than nitrites to hydrolysis, the role of nitrate ester may be to act as a "shield" to the organic nitrite until it is fed completely to endothelial cell.87,88

After being formed, nitrite ester is hydrolyzed to give a hydrogen group a molecule with alcohol and inorganic nitrite, which reacts with GSH in the presence of glutathione S-transferase to form nitroglutationa S- (GSNO). This capability also integrates the idea that the glutathione S-transferase can be involved through its ability to catalyze the formation of S-nitrosothiols from GSH and endogenous nitrite ester. Based on these observations, a possible mechanism in the bioactivation of organic esters to induce relaxation of cervix is ​​summarized in Figure 2 and described under the following events: 1) The nitrates ester (RONO2) are taken up by smooth muscles endothelial cells; 2) These ester compounds diffuse within the cell being reduced to organic nitrates by action of some proteins bound to the membrane such as flavoproteins; 3) Reaction between GSH and nitrite ester (RONO) to form GSNO is catalyzed by GSH S-transferase, and; 4) The GSNO releases NO molecules by a variety of biochemical mechanisms not described yet on human cervix.89,90

Oxide nitric donors drugs are not effective to induce cervical ripening in animal models.45 Although NO donors such as isosorbide mononitrate,56,91-95 sodium nitroprusside,96,97 and glyceryl trinitrate applied intravaginally or via intracervical induce cervical ripening at the end of human pregnancy.98,99 In general, NO donors appear to be less effective to dilate the cervix that PGs in viable pregnancies. However, in nonviable pregnancies initial isosorbide dinitrate (IDN) has been more effective and safer than misoprostol for cervical ripening.9 The IDN and other oxide nitric donors are safe and show no major adverse effects on fetus and mothers.28,91,100-104

2.4. JUSTIFICATION

The pharmacological stimulation of cervical ripening in women with late intrauterine death attempts to reduce the number of caesarean sections performed in the medical units of gynecological care. The current pharmacological method for promoting induction of cervical ripening is by using prostaglandins that are generally administered in the posterior fornix of vagina. Evidence has shown histological changes on cervix induced by misoprostol and gemeprost that are similar in proline incorporation by sample protein and the diameter of the collagen fibers in certain tissue biopsies. The action of prostaglandins seems to be in the connective tissue stroma, and evidence of disintegration and dissolution of collagen are supported by the results of intake proline.105 Prostaglandins are not free of adverse effects, maternal and fetal events, mainly because of its stimulatory effect on uterine contractions. After application of prostaglandins for induction of cervical ripening, 5% of women observed uterine hypertonus. During labour, uterine hypertonia is not only painful for the mother, but can also result in fetal distress that often requires emergency caesarean section. Tachysystole and uterine hypertension associated with abnormal patterns of fetal heart rate have also been determine.106 In addition, these drugs have been associated with a number of side effects such as nausea, headache, vomiting, diarrhea, fever, chills, abdominal and vaginal bleeding.

Nitric oxide (NO)-releasing drugs are a novel class of effective and safe agents for cervical ripening such as isosorbide dinitrate. Several chemical donors of NO are currently being used in various types of experimental and therapeutic studies.107 The NO donor, isosorbide mononitrate, is effective at inducing cervical ripening during the first trimester, prior to medical termination of pregnancy.108 Other NO donors, such as glyceryl trinitrate and sodium nitroprusside, administered during the first trimester, have fewer adverse effects than the prostaglandin analogue gemeprost.109 In contrast to the stimulatory actions of prostaglandins, activation of the NO system leads to myometrial relaxation and can be used to successfully treat intrapartum fetal distress caused by uterine hypertonus.110,111 A fall in maternal blood pressure, if severe, will compromise uteroplacental blood flow causing fetal hypoxia. Nevertheless, the risk of maternal hypotension is a potential problem when using an NO-releasing drug for cervical ripening due to its vasodilatory function. Induction of cervical ripening preoperative reduces morbidity in surgical termination of pregnancy, including those related to hemorrhage, incomplete emptying of the uterus, uterine perforation and cervical trauma.

2.5. OBJECTIVE AND HYPOTHESIS

2.5.1. OBJECTIVE OF EXPERIMENT

The main objective of our study is to compare the efficacy and adverse effects of the intravaginal administration of isosorbide dinitrate in gel form followed by a high dose of oxytocin for the induction of labour after late foetal death with a commonly utilised combined regimen, misoprostol-oxytocin. Also, we will establish adverse events such as blood pressure, respiratory rate, and temperature, as well as nausea, headache, vomiting, diarrhea, fever, chills, abdominal pain and vaginal bleeding in women treated with misoprostol or isosorbide dinitrate.

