**Haemodynamic stability:**

Heart rate (bpm)

Respiratory frequency (xminutes)

Core temperature (°C)

Systolic blood pressure (mmHg)

Diastolic blood pressure (mmHg)

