**Adverse effects:**

Headache

Abdominal pain

Pelvic pain

Lower back pain

Nausea

Dizziness

Vomiting

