4.5. DATA COLLECTION

Data of the treatment will discarded, and only the study number will used to code the patient’s measurements. The type of treatment remained unknown to the participating women, and at the end of study period the results will analysed. All participants were given a vaginal exam by the same person, who was blinded to the treatment allocation. The medications were administered in the posterior fornix, and cervical activity was evaluated at baseline and every 3 hours to monitor any change based on the Bishop score.

If the cervical conditions did not change after the treatment application, participants will receive a new dose, without exceeding 4 doses, to facilitate cervical ripening. Once a Bishop score of over 7 will reached, oxytocin will infused in a balanced electrolyte solution beginning with an infusion rate of 2 mIU/min and doubling the dose every 15 minutes. The labour induction time from the first application of medication to the expulsion of the foetus will determined with a digital stopwatch. Each woman's vital signs will verified to determine that she is in stable condition and demonstrated haemodynamic stability as a requirement for the application of a new dose. During this time, the data and medical information will collected on paper and will later entered into a computational database. The participants will remain at rest during the evaluation of adverse effects, such as headache, abdominal pain, pelvic pain, lower back pain, nausea, dizziness, and vomiting. The lack of cervical activity after 4 doses of medication will considered treatment failure.

4.6. PILOT STUDY.

The purpose of conducting the pilot study will be examine the feasibility of an clinical approach study. Our pilot study can be used to evaluate the feasibility of recruitment, randomization, retention of patients and assessment procedures of the novel intervention. Ten women with ultrasonographic diagnosis of fetal death above 20 weeks gestation will be randomly selected to receive the pre-induction treatment based isosorbide dinitrate gel solution or misoprostol gel solution. The time interval between the application of pretreatment, the optimal relaxation of the cervix and conduction of labor will be determined in women in each experimental group. Also, clinical data obtained from these patients will serve to estimate the required sample size. Patients will have access to the best proven therapeutic method identiﬁed by the study.

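### Diarrhoea, chills and vaginal bleeding are named in the objective but have no field in the protocol's variable list, and fever has only a temperature reading without a threshold

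*Protocol*

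**What the plan says.** Section 2.5.1 puts adverse effects beside efficacy in the main objective. It then states: "we will establish adverse events such as blood pressure, respiratory rate, and temperature", and continues "as well as nausea, headache, vomiting, diarrhea, fever, chills, abdominal pain and vaginal bleeding in women treated with misoprostol or isosorbide dinitrate". The safety objective thus has three vital signs and eight symptoms, to be established in both arms.

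Section 4.4 lists the variables to be recorded. Under "Adverse effects" it has seven items, for example "Lower back pain". Core temperature stands in a separate block on haemodynamic stability, with heart rate, respiratory frequency and blood pressure. Section 4.5 describes the procedure as "evaluation of adverse effects, such as headache, abdominal pain, pelvic pain, lower back pain, nausea, dizziness, and vomiting", which are the same seven items.

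Section 4.7 evaluates safety from the adverse-effect data by relative risks with 95% confidence intervals, compares signs and symptoms by chi-square, and compares haemodynamic data by the t test.

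Section 2.4 says that prostaglandins have been associated with "side effects such as nausea, headache, vomiting, diarrhea, fever, chills, abdominal and vaginal bleeding". Section 2.2 singles out three effects of misoprostol in particular, and vaginal bleeding is one of them.

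**The concern.** The objective and the list of variables do not match. A symptom with no variable cannot enter a relative risk or a chi-square test. A statistical analysis plan, which was not available for this review, could choose methods or set a fever threshold, but it cannot supply data that were never collected. These events happen during the hours of induction and would be hard to reconstruct reliably afterwards.

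The missing symptoms also matter by the protocol's own account. They are among the effects it attributes to the comparator's drug class, and vaginal bleeding is part of its stated reason for seeking an alternative to misoprostol. At stake is whether the trial can answer the whole of its own safety question.

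**Working it through.** The protocol calculates no figure on this point, so the check is a comparison of lists. The inputs are the symptoms in section 2.5.1, the variables in section 4.4 and the list in section 4.5.

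| Symptom in 2.5.1 | Adverse-effect item in 4.4 | Listed in 4.5 | Other variable in 4.4 |
|---|---|---|---|
| Nausea | yes | yes | not needed |
| Headache | yes | yes | not needed |
| Vomiting | yes | yes | not needed |
| Abdominal pain | yes | yes | not needed |
| Fever | no | no | core temperature |
| Diarrhoea | no | no | none |
| Chills | no | no | none |
| Vaginal bleeding | no | no | none |

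**Counts**
- Symptoms in the objective: 8. Adverse-effect items: 7. In both lists: 4.
- In the objective but not among the adverse-effect items: 8 − 4 = 4.
- Of these, derivable from another recorded variable: 1 (fever). With no variable at all: 4 − 1 = 3, which is 3/8 = 37.5%.
- Among the adverse-effect items but not in the objective: 7 − 4 = 3 (pelvic pain, lower back pain, dizziness).
- Vital signs named in the objective and recorded: 3 of 3.

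**Fever.** Core temperature sits in the haemodynamic block, and section 4.7 assigns haemodynamic data to the t test. Read literally, temperature would be compared as a mean. Without a stated rule for turning readings into fever yes/no, fever does not enter the relative-risk or chi-square comparison either.

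**Who the missing items concern.** Section 2.4 attributes all three missing symptoms, and fever, to prostaglandins. Section 2.2 attributes vaginal bleeding to misoprostol specifically; the other two effects it stresses, nausea and abdominal pain, are recorded.

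**Can a direction of bias be derived?** Section 2.5.2 predicts one leading adverse effect per arm: headache for the nitrate and pelvic pain for misoprostol. Both are recorded. Of the effects in section 2.4, nausea, headache and vomiting are also recorded. Headache is therefore tied to both drug classes. No section gives an adverse-effect rate by arm for any missing item. The comparator's harm could be under-recorded, but no direction or size follows from the document.

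**The case against.** **The list is open.** Section 4.5 introduces its seven effects as examples, so staff may record others. This stands in part: the procedure is not expressly limited to seven. But section 4.4 is a plain list with no field for other effects, and unprompted reports do not support a relative risk for each symptom.

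**Fever is covered.** This largely stands. Temperature is recorded, and section 2.5.1 itself names it as a safety measure. Only the rule for deriving fever is missing, and an analysis plan could supply it. A reader who compares only the two symptom lists might count four missing effects; the supported count is three.

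**Most of the comparison survives.** This stands. Four of the eight symptoms and all three vital signs can be compared. A reader might infer that the safety comparison as a whole cannot be made, but that is true only of the three uncollected items.

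**The leading outcomes are untouched.** This stands. Section 4.4 sets foetal expulsion within 15 hours as the main result and the administration-to-induction interval as the secondary one. Neither depends on these fields.

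**Conclusion.** The inconsistency is real and limited. Three of the eight symptoms in the objective have no variable, and a fourth, fever, has a measurement but no definition. The planned safety analysis cannot cover the three and could understate comparator harm. The point deserves correction because adverse effects belong to the main objective and uncollected data cannot be recovered. It is not a critical flaw: the main outcome, the secondary outcome and the sample size of 30 per group do not change.

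The conclusion assumes that section 4.4 reflects the paper form actually used; the form itself is not in the document.

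Two stronger readings are tempting and are not supported:
- **That the form leans against the nitrate arm.** Several effects that the protocol links to misoprostol or prostaglandins are recorded, including pelvic pain, the one it predicts for misoprostol. Dizziness is recorded too, but no section ties it to nitrates. There are no rates by arm from which to derive a lean.
- **That uterine hypertonus and tachysystole are also wrongly omitted.** Section 2.4 does say "After application of prostaglandins for induction of cervical ripening, 5% of women observed uterine hypertonus", but neither event is named in the objective, so their absence contradicts nothing. The 5% refers to prostaglandins in general, not to this preparation or population. The 3-hourly assessment in section 4.5 is described as a Bishop-score examination, with no monitoring of uterine tone, so collecting these events would not simply be an extra field.

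**What to change.** Make sections 2.5.1, 4.4 and 4.5 agree:

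1. Add diarrhoea, chills and vaginal bleeding as yes/no items to the adverse-effect block of section 4.4 and to the list in section 4.5, recorded in both arms over the same period as the existing items.
2. State, in the protocol or the analysis plan, how fever is derived from the core temperature already recorded.
3. In section 4.7, include these four in the relative-risk and chi-square analyses already planned.

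The cost is three more fields on the paper form and one definition. No new visit, procedure, change in treatment or increase in sample size is needed. The change should be in place before enrolment. If collection has already begun with the seven-item list, the report should say that the three symptoms were not systematically recorded up to the date of the change.

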2.5.2. HYPOTHESIS OF EXPERIMENT

It is expected that the 97% probability of achieving successful cervical ripening (Bishop score of over 7) with 80 mg of isosorbide dinitrate gel solution at 12 hours and a 67% chance of achieving successful cervical ripening with 100 mcg of misoprostol (power of 80%, α-value of 0.05, and β-value of 0.2) with 25% of all women whose will fail to induce labour. The main adverse effect associated with the administration of isosorbide dinitrate gel solution will be the headache and women treated with misoprostol will report preferably pelvic pain.

**3. DESIGN OF EXPERIMENTS**

3.1. PLANNING EXPERIMENT

EXPERIMENTAL STUDY _X_

CUASI-EXPERIMENTAL STUDY ___

OBSERVACIONAL STUDY ___

